## 6. Methods: Data Collection, Management, and Analysis

### 6.1. Data Collection Methods

The following health information will be obtained from the patients’ medical records after written informed consent has been obtained: diagnosis, date of diagnosis, anatomical location of the primary tumor, age, sex, TNM classification, UICC stage, treatment modality, dates of treatment initiation and completion, recurrence status, comorbidities, complications, previous or concurrent malignancies, performance status, smoking status, pack year history, weekly alcohol consumption, HPV and p16 status of the primary tumor and lymph nodes (including date of analysis and HPV genotype), histopathological diagnosis and morphological characteristics, imaging findings, status at the last clinical examination, date of subsequent follow-up visits, and vital status, including the date and cause of death.

Blood samples will be collected at the time of diagnosis (baseline), two months after completion of treatment, and every six months thereafter for a minimum of two years and up to three years. Each sample will be analyzed for ctHPV-DNA corresponding to the HPV genotype identified in the patient’s primary tumor. HPV genotyping on primary tumors and lymph nodes is performed using the Zytovision VisionArray HPV Chip at the Department of Pathology as part of the routine diagnostic work-up.

The blood samples are collected in Streck Cell-Free DNA BCT CE tubes. These tubes are designed to stabilize blood cells and prevent the release of genomic DNA for up to 7 days at room temperature, thereby minimizing contamination of cell-free DNA and enabling the extraction of high-quality cell-free DNA. Samples will be stored at room temperature for up to four days before processing. Approx. 8 mL plasma/patient (corresponding to two Streck Cell-Free DNA BCT CE tubes) will be isolated by centrifugation at 2250× *g* for 10 min. The isolated plasma will subsequently be centrifuged at 16,800× *g* for 10 min to remove any residual cells or cellular debris before storage at −80 °C. DNA will be extracted using the QIAamp Circulating Nucleic Acid Kit (#55114) on a QIACube instrument and eluted in 60 µL. DNA concentration and purity will be assessed using NanoDrop (Thermo Fischer Scientific, Waltham, MA, USA) or TapeStation (Agilent Technologies, Santa Clara, CA, USA). The following quality control (QC) assays will be used: QC assay 1. DNA purification efficiency will be assessed at the batch level by analyzing five healthy donor plasma samples spiked with the 191-bp CPP1 DNA spike-in before and after each batch of patient samples, instead of adding CPP1 DNA directly to the individual patient samples, allowing estimation of the mean DNA loss during extraction [20]. Batch-level controls were chosen instead of sample-level spike-in controls to avoid introducing exogenous DNA into individual clinical samples while preserving native patient DNA for future analyses. QC assay 2. Genomic DNA contamination (white blood cell contamination) will be assessed in native patient DNA as previously described [12] or using TapeStation. QC assay 3. Sample fragmentation will be assessed in native patient samples as previously described. All QC assays adhere to the guidelines published by the Danish ctDNA Research Center [12,21]. The amount of HPV-DNA in plasma and the specific HPV genotype will be assessed by our ultrasensitive droplet digital PCR (ddPCR) assay, which we have developed to assess eight high-risk HPV genotypes: HPV16, 18, 31, 33, 35, 45, 51, and 58 [12,15,16]. First, each sample will undergo a 12-cycle PCR pre-amplification containing only one HPV primer set together with the EMC7-65 primer set. Second, ddPCR analysis will be performed using the same HPV and EMC7-65 primer set (final concentration 900 nM) together with the corresponding probes (final concentration 250 nM). A sample is considered ctHPV-DNA positive when at least five HPV+ droplets are detected for the relevant HPV genotype. Samples with 5–20 HPV+ droplets, corresponding to results close to the analytical detection limit, will be confirmed using a second blood sample to minimize false-positive and false-negative results. If the second blood sample confirms HPV-DNA positivity, the sample is classified as positive. If the second blood sample is negative, the result is considered discordant, and the first blood sample is re-analyzed. The analytical limit of detection (LOD) has been internally defined as the lowest HPV-DNA concentration corresponding to five HPV+ droplets in the ddPCR analysis, corresponding to 1.9 double-stranded HPV-DNA copies/mL plasma. No formal limit of quantification (LOQ) has been established, as the assay was developed for sensitive detection rather than precise quantification at very low copy numbers. ddPCR runs were considered invalid in cases of failed droplet generation, insufficient accepted droplet count, positive droplets in the negative control, failed positive controls, or insufficient EMC7 amplification, indicating an inadequate sample quality. Samples with evidence of excessive genomic DNA contamination or poor cfDNA fragmentation quality were repeated or excluded from further analysis. The ddPCR assay is conducted at MDxCore, Department of Clinical Biochemistry, Copenhagen University Hospital—Rigshospitalet.

### 6.2. Data Management

Data will be stored on site in a secure REDCap web database [22,23]. The project leader and study investigators will be responsible for verifying the accuracy and completeness of the data.

### 6.3. Statistical Methods

The primary outcome, namely the sensitivity and specificity of ctHPV-DNA for detecting recurrence, will be calculated with 95% confidence intervals. Sensitivity will be determined among patients who develop recurrence, and specificity among patients who remain recurrence-free during follow-up. Positive predictive value will be determined among patients with positive ctHPV-DNA samples, and negative predictive value among patients with negative ctHPV-DNA results.

Only recurrence confirmed by a clinical and/or radiological examination will be regarded as recurrence. Histopathological confirmation will be included in the clinical verification if tissue sampling is feasible during the clinical examination.

The primary analyses will include all enrolled patients with a ctHPV-DNA baseline blood sample and at least one post-treatment blood sample, and follow-up assessment. Patients will be analyzed according to their clinical follow-up data, irrespective of the completeness of subsequent blood sampling or imaging, to minimize bias and reflect a real-world clinical practice.

Time-to-event outcomes, including time to recurrence detected by ctHPV-DNA and time to recurrence detected by clinical and/or radiological examination, will be analyzed using Kaplan–Meier survival curves. Median time to recurrence and corresponding 95% confidence intervals will be reported. Comparisons between ctHPV-DNA detection and standard surveillance will be performed using the log-rank test.

Healthcare utilization endpoints, including the number of PET/CT scans and Cancer Fast-Track referrals without evidence of recurrence, will be summarized using descriptive statistics (mean, median, standard deviation, and interquartile range). Between-group comparisons (e.g., patients with versus without recurrence) will be performed using *t*-tests for normally distributed variables or Mann–Whitney U tests for non-parametric distributions.

Analyses will use all available data, and, where appropriate, missing data will be handled using multiple imputation under the assumption that data are missing at random (MAR).

Sensitivity analyses will explore the impact of departures from the MAR assumption. For example, alternative imputation strategies may be applied, such as assuming that patients lost to follow-up either did or did not experience recurrence. These analyses will allow assessment of the robustness of estimates for sensitivity, specificity, time to recurrence, healthcare utilization, and patient-reported outcomes.

If the results from the sensitivity analyses are consistent with the primary analyses, confidence in the validity and generalizability of the findings will be strengthened. All statistical measures of uncertainty, including 95% confidence intervals and *p*-values, will be interpreted in the context of potential bias introduced by missing data.

Patient-reported quality of life (QoL), measured using the Danish version of the Fear of Cancer Recurrence Questionnaire (short form), will be evaluated as the change between follow-up visits. Each questionnaire item is rated on a five-point Likert scale (0–4) and summed into a total score. Total questionnaire scores will be reported, and within-patient changes will be assessed using the Wilcoxon signed-rank test. For repeated measurements over time, mixed-effects models using restricted maximum likelihood estimation will be employed, with patient ID as a random effect and time points as a fixed effect.

Exploratory analyses will include correlations between ctHPV-DNA levels and clinical outcomes, including recurrence, time to recurrence, and QoL scores. Spearman’s rank correlation coefficient will be used for non-parametric data. All tests will be two-sided, and a *p*-value < 0.05 will be considered statistically significant. All analyses will be conducted in R-studio.

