### 3.4. Outcomes

The primary endpoint is to evaluate the sensitivity and specificity of ctHPV-DNA for the detection of recurrence in patients with HPV+ OPSCC, using clinically or radiologically verified recurrence as the reference standard. Time frame: A minimum of two years and up to three years after completion of primary treatment. Sensitivity will be calculated among patients who develop recurrence, whereas specificity will be calculated among patients who remain recurrence-free.

Secondary endpoints are defined as follows:Time to recurrence detected by ctHPV-DNA.Time to recurrence detected by clinical and/or radiological examination.Number of referrals to Cancer Fast-Track examinations based on a positive ctHPV-DNA test result without evidence of recurrence.Number of PET/CT scans performed because of a positive ctHPV-DNA test result without evidence of recurrence.

Quality of life (QoL), assessed using the Danish version of the Fear of Cancer Recurrence Questionnaire (short form), will be completed by patients after receiving the result of each blood sample.

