### 4.1. Sample Size

The sample size was estimated using a diagnostic accuracy study sample size calculator based on the methodology described by Akoglu et al. [19]. The calculation was based on an expected sensitivity of 95%, an expected specificity of 95%, a disease prevalence of 11%, a two-sided type I error rate of 5% (corresponding to a 95% confidence interval), and a margin of error of 10%. Based on these assumptions, a minimum of 167 patients was required. With an expected disease prevalence of 11%, this corresponds to approx. 18–19 patients with residual disease or recurrence and 148–149 patients without disease. To account for potential dropout, loss to follow-up, and non-evaluable samples, the target sample size was increased to 200 patients.

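### Serial ctHPV-DNA samples are reduced to patient-level sensitivity, specificity, PPV and NPV without a patient-level positivity rule or a time link between a positive and a verified recurrence

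*Protocol article*

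**What the plan says.** All references are to the protocol article.

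- **Denominators (3.4 and 6.3).** Sensitivity is taken among patients who recur and specificity among those who stay recurrence-free. Section 6.3 adds: "Positive predictive value will be determined among patients with positive ctHPV-DNA samples", and "negative predictive value among patients with negative ctHPV-DNA results".
- **Positivity (6.1).** The five-droplet threshold and the confirmation step for 5–20 droplets classify a sample, not a patient.
- **Schedule.** Figure 1 gives samples at 2, 6, 12, 18, 24, 30 and 36 months after treatment. Section 3.3, read literally, gives 2, 8, 14, 20, 26 and 32 months. An unexplained positive adds a repeat at three months.
- **Follow-up (3.4).** "Time frame: A minimum of two years and up to three years after completion of primary treatment".
- **Analysis set (6.3).** A baseline sample, one post-treatment sample and a follow-up assessment are enough.
- **Unexplained positives.** If work-up and the repeat show no recurrence, the patient returns to standard follow-up (Section 4). Section 3.4 counts the resulting referrals and PET/CT scans as secondary endpoints.
- **Planning (4.1).** "a minimum of 167 patients was required", on sensitivity and specificity of 95% each. "With an expected disease prevalence of 11%, this corresponds to approx. 18–19 patients with residual disease or recurrence".

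**The concern.** A diagnostic 2×2 table needs one test result and one disease status per patient. The article fixes the disease status but leaves the test result open across several samples. Three consequences follow.

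1. **Overlap.** A patient who is negative at 2 months, positive at 12 months and then has a verified recurrence fits both the PPV and the NPV group.
2. **No time link.** Take a patient who is positive at 2 months, has a clear work-up and repeat, and recurs at 30 months. By final status this patient is in the sensitivity denominator, and nothing stops the early positive from counting as detection. The secondary endpoints count that same positive as a false alarm.
3. **Unequal exposure.** If any positive makes a patient positive, a recurrence-free patient with seven samples has more chances of a false positive than one with a single sample. Specificity then partly measures length of follow-up and attendance.

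Sensitivity and specificity are the primary endpoint. Results are unblinded, and a one-year interim analysis will be published, so the classification should be fixed before results accumulate.

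**Working it through.** **Step 1. Reproduce the planned size.** Inputs from 4.1: sensitivity and specificity 0.95, prevalence 0.11, margin 0.10, z = 1.96.
- Diseased patients: 1.96² × 0.95 × 0.05 / 0.10² = 18.25.
- Total: 18.25 / 0.11 = 165.9, so 166, against 167 stated.
- Split: 167 × 0.11 = 18.4 and 167 × 0.89 = 148.6, as stated.

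The formula uses one classification per patient. The 95% values are therefore in effect per patient, although 4.1 does not say so.

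**Step 2. Samples per patient.** Figure 1 gives 5 by 24 months and 7 by 36 months. Section 3.3 gives 4 and 6. The analysis set allows as few as 1.

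**Step 3. NPV under two readings.** Take 167 patients: 19 recur (18 detected) and 148 do not (141 never positive).
- Any negative qualifies, every patient having at least one: 148/167 = 88.6%.
- Only never-positive patients qualify: 141/(141 + 1) = 99.3%.

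The first figure is the extreme case. If a share f of recurring patients had an earlier negative, NPV = 0.89/(0.89 + 0.11f):

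| f | NPV |
|---|---|
| 0.5 | 94.2% |
| 0.7 | 92.0% |
| 0.9 | 90.0% |
| 1.0 | 89.0% |

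Assume exponential recurrence times with the cited median of 12–18 months, and a lead time of 0–4 months (Section 1.1 reports up to four). The share still negative at 2 months is then 0.5^((2 + lead)/median), or 0.71 to 0.93. That puts NPV at about 90–92%.

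**Step 4. Sensitivity without a time link.** Planning case: 18/19 = 94.7%. If one of the 18 detections rests only on a remote positive, the time-linked value is 17/19 = 89.5%. Each such patient moves the estimate by 1/19 = 5.3 points, and two move it by 10.5, against a planned margin of 10. The average effect is smaller, because only recurrences with no timely positive can gain. With 5% of recurrences truly missed, three earlier samples and an assumed per-sample specificity of 95%, it is 0.05 × (1 − 0.95³) = 0.7 points. It grows if the test misses more.

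**Step 5. Specificity and number of samples.** Under an any-positive rule with independent samples, patient-level specificity is s^k for per-sample specificity s and k samples. Both values of s are assumptions.

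| s | k = 1 | k = 5 | k = 7 |
|---|---|---|---|
| 95% | 95.0% | 77.4% | 69.8% |
| 99% | 99.0% | 95.1% | 93.2% |

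For s = 95% and k = 7, an assumed within-patient correlation of 0.1, 0.3 or 0.5 (beta-binomial) gives 75.9%, 83.1% or 87.7%. To reach 95% per patient with independent samples, s must be 0.95^(1/5) = 98.98% for five samples or 0.95^(1/7) = 99.27% for seven. Positive correlation lowers that requirement.

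**The case against.** The strongest reply is that this is detail for an analysis plan that is not shown. A patient-level rule, a window and clustered intervals are commonly placed there. That would hold if the article were silent, but it commits to denominators and to classification by final status, and those commitments overlap as worded.

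The work-up, the three-month repeat and the secondary counts of referrals and scans do deal with unexplained positives. They govern management and resource use, however, and do not say which cell of the accuracy table the patient enters.

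Two stronger conclusions are tempting and are not supported.

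- **A reader might infer that the NPV rule must give a wrong answer.** It need not. In a patient-level table, test-negative is naturally the complement of test-positive, so never positive is the likely intention. The PPV wording, taken equally literally, would admit the roughly 97% of patients expected to be positive at baseline, which cannot be meant. NPV is also not a listed endpoint in 3.4. The fault is that the text allows both readings.
- **A reader might infer that 40–54 of 178 recurrence-free patients (0.89 × 200) will be false positives, rather than about 9.** Those counts are 178 × (1 − 0.774) and 178 × (1 − 0.698). They require the 95% to be per sample and the samples to be independent. The arithmetic of 4.1 points to a per-patient value, samples may be correlated, and low-droplet results are confirmed on a second blood sample.

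It is also fair that cumulative specificity falls with repeated testing under any such surveillance rule. That is not an error, but it has to be visible in the definition and in the planning value.

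**Conclusion.** The point holds as a defect in how the primary endpoint and the predictive values are defined. The documents give no patient-level positivity rule and no time link, while fixing patient denominators by final status.

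The size is up to about 10 points of NPV between the two readings in the planning case, or about 5 points if only half of recurring patients had an earlier negative. For sensitivity it is 5.3 points for each recurrence credited to a remote positive, with a small average effect if true sensitivity is near 95%. For specificity the effect depends on per-sample performance and correlation, neither of which the documents give. With seven independent samples, 95% per patient needs about 99.3% per sample.

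The NPV figures assume the planning values. The specificity figures assume an any-positive rule; a last-sample or per-sample rule would behave differently. The sample-size calculation itself reproduces and is not in question here.

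**What to change.** **In 6.3:**

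(a) Use post-treatment samples only. Define test-positive as at least one finally positive sample up to verification or end of follow-up, and test-negative as all samples negative.

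(b) For sensitivity, count a recurrence as detected only if a positive falls within a pre-specified window before or at verification. The sponsor should choose and justify the length and give a second length as a sensitivity analysis. Count a recurring patient whose only positives lie outside the window as missed, and state where that patient sits in the patient-level PPV and NPV. State how positives too close to the end of follow-up to be resolved are handled.

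(c) Add per-sample specificity, PPV and NPV, judging each sample against verified recurrence before the next scheduled sample, with patient-clustered confidence intervals (GEE or bootstrap).

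**In 4.1:** state that the 95% values are per patient over the whole schedule, as the 167-patient arithmetic implies, and note the per-sample specificity this requires.

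**Cost:** a few sentences and a little more analysis, with no new data. Reported sensitivity may be slightly lower.

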## 1. Introduction

### 1.1. Background

Approximately 1600 patients are diagnosed with head and neck cancer (HNC) in Denmark annually, and the incidence is increasing [1]. Oropharyngeal squamous cell carcinoma (OPSCC) constitutes one of the largest subgroups of HNC and the fastest-increasing incidence [1]. This increase is primarily driven by the rising incidence of human papillomavirus-positive (HPV+) OPSCC [2,3,4,5,6,7], which now accounts for up to 70% of all OPSCC cases in Denmark [2]. Compared with HPV-negative (HPV−) OPSCC patients, patients with HPV+ OPSCC have a distinct clinical profile, and their tumors differ both molecularly and histopathologically. HPV is a group of double-stranded DNA viruses [8], and several different high-risk genotypes exist. The most prevalent genotypes in OPSCC in Denmark are HPV16, HPV33, HPV35, HPV18, and HPV45 [2]. HPV+ patients are typically younger, have fewer comorbidities, and have a better prognosis than HPV-patients [9,10]. Despite this, 10–15% of patients with HPV+ OPSCC experience recurrence despite successful treatment, and 30% die within 5 years of diagnosis [11]. In Denmark, all patients, regardless of HPV status, treatment modality, or disease stage, follow the same standardized clinical follow-up program to facilitate early detection of recurrence. However, detecting recurrence remains challenging, as it relies on either visible findings during clinical examination or symptoms reported by the patient.

A previous study from our department demonstrated that circulating tumor HPV-DNA (ctHPV-DNA) was detectable at the time of diagnosis of HPV+ OPSCC with a sensitivity of 97%, and that ctHPV-DNA levels decreased after treatment [12]. In patients whose primary treatment was successful, ctHPV-DNA levels dropped below the limit of detection, whereas ctHPV-DNA could still be detected in the blood of patients with residual disease [12]. Reappearing ctHPV-DNA was detected in patients with recurrence up to four months before recurrent disease was diagnosed clinically [12]. These findings suggest that ctHPV-DNA testing may detect recurrence earlier than conventional clinical examination, thereby enabling earlier diagnosis and potentially earlier intervention. However, these findings require validation in a prospective setting.

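### The promised Kaplan–Meier median time to recurrence will not be reached in the whole cohort at the protocol's own 11% recurrence; report cumulative incidence at fixed times instead

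*Protocol article*

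**What the plan says.** Section 3.4 lists two time-to-recurrence secondary endpoints: one by ctHPV-DNA, one by clinical or radiological examination. Section 6.3 assigns Kaplan–Meier curves to both and then states: "Median time to recurrence and corresponding 95% confidence intervals will be reported". No other numerical summary is named for them, and the sentence is not restricted to patients who recur. Only verified recurrence counts as recurrence. Section 6.3 does not say how deaths enter these curves, although section 6.1 collects the date and cause of death.

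The expected frequency of the event is given twice. Section 4.1 assumes "an expected sensitivity of 95%, an expected specificity of 95%, a disease prevalence of 11" percent, a figure that covers residual disease as well as recurrence. Section 1.1 says that 10–15% of patients "experience recurrence despite successful treatment, and 30% die within 5 years of diagnosis". Follow-up lasts two to three years after treatment (sections 3.3 and 4).

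Section 6.3 also states: "Exploratory analyses will include correlations between ctHPV-DNA levels and clinical outcomes, including recurrence, time to recurrence, and QoL scores". It names Spearman's coefficient for non-parametric data and does not say which patients enter the correlation with time to recurrence.

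**The concern.** A Kaplan–Meier median is the time at which the estimated event-free proportion falls to 0.50. If about one patient in nine has the event, the curve stops far above that level. The only number promised for two secondary endpoints would then be a blank, and so would its confidence interval. A summary chosen after the data are seen would carry less weight than one fixed now.

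The problem would show first at the interim analysis, which section 7.1 commits to publishing once all patients have one year of follow-up.

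The exploratory correlation has a related gap: about 89% of patients will have no observed recurrence time, and a rank correlation cannot use a censored time.

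**Working it through.** **Inputs from the protocol article.** Sensitivity and specificity 95%, prevalence 11%, margin 10 points, two-sided 5%, minimum N 167, target N 200 (section 4.1). Recurrence 10–15% (section 1.1). Follow-up 24–36 months, and a reported median time to recurrence of 12–18 months (section 4).

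**1. The plan's own figure.** Patients with disease needed: 1.96² × 0.95 × 0.05 / 0.10² = 18.25. Total: 18.25 / 0.11 = 165.9, so 166 against the stated 167. The split also agrees: 167 × 0.11 = 18.4 and 167 × 0.89 = 148.6. The 11% is therefore the rate on which the study is built. At N = 200 it gives 200 × 0.11 = 22 events; 10–15% gives 20–30.

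**2. Where the curve ends.** Ignoring deaths, about 1 − 0.11 = 0.89, with a range of 0.85–0.90. Reaching 0.50 would take events in roughly half the cohort, about 100 of 200.

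**3. The confidence interval.** The interval for a median is read off where the confidence band crosses 0.50. Simple lower limits at N = 200, ignoring censoring:

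| Curve ends at | SE = √(S(1−S)/200) | Lower limit = S − 1.96 SE |
|---|---|---|
| 0.89 | 0.022 | 0.85 |
| 0.85 | 0.025 | 0.80 |

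Neither is near 0.50, so the interval has no finite limits either.

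**4. Simulation.** N = 200, 2,000 runs per scenario. Assumptions not given in the documents: truncated exponential recurrence times, censoring uniform over 24–36 months, and recurrence-free deaths of 0, 15 or 30% at five years. At 11% recurrence the curve reached 0.50 in at most 0.05% of runs. Across 10–20% recurrence it did so in at most 0.1%, and the lower confidence limit reached 0.50 in at most 1.5%.

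**5. The ctHPV-DNA endpoint.** Suppose every positive test counted as an event. With 95% specificity per patient, the ever-positive share is 0.11 × 0.95 + 0.89 × 0.05 = 14.9%. With 95% specificity per sample and independent errors, it is 0.11 × 0.95 + 0.89 × (1 − 0.95⁶) = 34.0% over six post-treatment samples, and 37.3% over seven. All are below 50%.

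**6. Interim analysis.** If the median among recurrers is 12–18 months, at most about half of the recurrences fall in the first year. The curve at 12 months is then about 1 − 0.5 × 0.11 = 0.945 or higher.

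**7. Recurrers only.** A median can be computed. Its exact 95% interval runs from the 5th to the 14th ordered time with 18 patients, and from the 6th to the 17th with 22.

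**8. Effect of deaths.** In the simulation at 11% recurrence, the 24-month estimate from Kaplan–Meier with deaths censored, against cumulative incidence, is:

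| Recurrence-free deaths at 5 years | Median 12 months among recurrers | Median 18 months among recurrers |
|---|---|---|
| 15% | 9.45% vs 9.22% | 8.80% vs 8.56% |
| 30% | 9.36% vs 8.87% | 8.84% vs 8.33% |

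The gaps are 0.2 to 0.5 points. A separate constant-hazard calculation at 36 months gives 11.5–11.7% against 11.0%, a gap of 0.5–0.7 points. For comparison, the 95% half-width for 22/200 is 1.96 × √(0.11 × 0.89 / 200) = 4.3 points.

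**The case against.** The strongest reply is that the authors mean the median among patients who recur. Section 4 uses the term in that sense: at 10–15% recurrence, a reported median of 12–18 months can only describe recurrers. Section 3.4 likewise computes sensitivity among patients with recurrence. This has force, and it rules out one stronger reading. A reader might infer that the endpoints cannot be estimated or have no reportable result. That goes too far: the Kaplan–Meier curves can be shown in any case, and a median among about 18–22 recurrers can be calculated.

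The reply does not settle the matter. Section 6.3 never states the restriction. Its sensitivity analyses assume that patients lost to follow-up did or did not recur, and they list time to recurrence among the estimates tested, which fits a whole-cohort analysis better. A recurrers-only median also selects on the outcome, so it describes and does not estimate risk over time.

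Three further replies are largely right.

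- **Deaths.** A reader might subtract 10–15% from 30% and conclude that at least 15–20% of study patients die without recurrence. This does not follow. Section 1.1 counts recurrence after successful treatment, so deaths from residual disease fall outside it. It gives no time horizon for recurrence and does not say that its mortality excludes palliative patients, whom section 3.2 excludes. That deaths would be censored is itself an inference, and the numerical effect is small.
- **Spearman.** The analysis is exploratory and valid among patients with an observed recurrence time. The text does not say that end of follow-up will be entered as a recurrence time.
- **Lead time.** The aim in section 1.2 concerns earlier detection, which cumulative incidence does not measure within a patient. The times among recurrers should therefore stay in the report.

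**Conclusion.** The point holds as a defect in the chosen summary statistic. On the protocol's 11%, or its 10–15%, the whole-cohort median and its 95% CI will not be reached for either endpoint. This rests on the protocol's event rates and on reading section 6.3 as written, with all analysed patients included. It does not depend on the simulation's assumptions, because recurrence would have to be several times the planned rate before the curve approached 0.50. If recurrers alone are meant, the defect is an unstated population and the remedy is still a change of text.

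The handling of deaths adds about 0.2–0.7 points and would not justify a change alone. It comes at no extra cost with the replacement summary. Kaplan–Meier handles ordinary censoring correctly, and the sample size and primary endpoint are unaffected.

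**What to change.** In section 6.3:

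- Replace the median as the summary of both time-to-recurrence endpoints with the cumulative incidence of recurrence at fixed times, for example 12, 24 and 36 months after treatment, with 95% CIs. Show the numbers at risk, because only part of the cohort may be followed to 36 months.
- Count death without recurrence as a competing event (Aalen–Johansen estimator).
- Report the median and range of time to recurrence among recurrers only, with their number, labelled as descriptive.
- State that the exploratory Spearman correlation with time to recurrence includes only patients with an observed recurrence. A Cox model with time-updated ctHPV-DNA is not required: it would rest on about 22 events, and a positive test itself triggers the examinations that verify recurrence.

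The cost is wording. Dates and causes of death are already collected, and no visit, sample or patient is added. The change should be made before the one-year interim analysis.
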